### Sample Size

Based on the recommendations of Whitehead et al [57], for a pilot trial with 90% power and a 2-sided significance level of 5%, the suggested sample size per treatment arm based on previous literature with a medium effect size (0.43) [58] is 25. Hence, a total of 72 participants (36 participants per arm) was required after taking into consideration a 30% nonresponse rate.

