## Methods

### Type and Design

This study is a single-blind, pilot randomized controlled trial with participants randomized using a 1:1 ratio.

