### Statistical Analysis

Data will be analyzed using SPSS version 26, and significance is set at *P*<.05. Intention-to-treat analysis will be used. Categorical variables will be presented as the frequency and percent values, while continuous data will be presented as mean (SD). Baseline between-group comparisons will be conducted using Pearson chi square and Fisher exact tests for categorical data. Meanwhile, independent *t* tests will be used for continuous data. Repeated measures ANOVA will be used for within-group (time effect) and between-group (treatment effect) comparisons at 6 weeks. The mean difference and its corresponding 95% CI will be reported, with the significant level set at *P*<.05.

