Nevertheless, certain challenges remain. First, the reliance on self-reported measures may introduce bias, as participants may underreport symptoms due to stigma or discomfort. Second, as demonstrated with other mHealth interventions like the Happy Mother app, user engagement can be inconsistent, and low adherence rates may diminish the overall effectiveness of the intervention​ [77]. To address this, the LoVE4MUM app incorporates strategies to enhance user engagement, such as push notifications, scripts, and personalized feedback. Another critical aspect to consider is the influence of cultural factors on app engagement and perception, which may affect how Malaysian mothers interact with the app. Ensuring that the app’s content is culturally sensitive and tackles common misconceptions about PPD will be essential in maximizing its impact. Moreover, as a pilot trial, the sample size may not allow for definitive conclusions, and the study’s findings should be interpreted as preliminary evidence of the app's potential.

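### The Sample Size section ties 90% power to this pilot of 25 mothers per arm; with 0.43 read as a standardised mean difference, a two-sample comparison has about 32%

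*Protocol article*

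**What the plan says.** The article's Sample Size section is the only justification for the size of the trial. Citing a recommendation for pilot trials, it says that "for a pilot trial with 90% power and a 2-sided significance level of 5%, the suggested sample size per treatment arm" is 25, "based on previous literature with a medium effect size (0.43"). It then says that "a total of 72 participants (36 participants per arm) was required after taking into consideration a 30% nonresponse rate". It mentions no later definitive trial and gives neither a scale nor a standard deviation for 0.43.

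The Abstract makes the app's effectiveness against postpartum depression the primary outcome, and the Measurements section measures it with the EPDS. The Statistical Analysis section plans repeated measures ANOVA and states: "The mean difference and its corresponding 95% CI will be reported, with the significant level set at" P<.05. The Discussion (Overview) adds that "as a pilot trial, the sample size may not allow for definitive conclusions" and calls the findings preliminary. It gives no power figure and does not return to the 90%.

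**The concern.** A reader will take the sentence at face value: this pilot, at 25 evaluable mothers per arm, has a 90% chance of detecting an effect of 0.43 at the two-sided 5% level. If its chance is nearer one in three, two errors become possible when the results appear.

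- A non-significant EPDS difference could be taken as good evidence against the app, although that is the likelier result even if the assumed effect is real.
- A significant difference would have to be larger than the effect assumed, so its size could be carried over too optimistically into the design of the next trial.

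**Working it through.** **Inputs.** Two-sided 5%, 90% power, effect size 0.43, 25 per arm, 30% nonresponse and 36 per arm come from Sample Size; 1:1 allocation from Type and Design; three measurement times (baseline, 1 week, 6 weeks) from the measurement sections. Assumptions: 0.43 is a standardised mean difference d (SD = 1), and the correlation ρ between visits, which is not given, is shown as a range.

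**1. The plan's own figures.** The inflation step reproduces: 25 / 0.7 = 35.7, rounded up to 36. Since 36 × 0.7 = 25.2, the plan expects about 25 evaluable mothers per arm.

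The 25 does not reproduce from the stated power, alpha and effect size:

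n per arm = 2 (1.960 + 1.282)² / 0.43² ≈ 114 (115 with the t distribution). After 30% loss, 115 / 0.7 = 164.3, so 165 per arm.

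**2. Power of the design as stated.** Two-sample t test, noncentrality d√(n/2):

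- n = 25: 0.43 × √12.5 = 1.520, critical t (48 df) = 2.011, power 31.9%.
- n = 36: 0.43 × √18 = 1.824, critical t (70 df) = 1.994, power 43.6%. This needs all 72 mothers to supply data.

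The d detectable with 90% power is about 0.94 at 25 per arm and 0.77 at 36.

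**3. Precision.** The 95% CI half-width is t × √(2/n) SD: 2.011 × √(2/25) = 0.57 SD at 25 per arm and 1.994 × √(2/36) = 0.47 SD at 36. At 25 per arm an unadjusted difference must therefore exceed 0.57 SD to be significant, at least 0.57 / 0.43 = 1.3 times the assumed effect.

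**4. Baseline adjustment.** The residual SD is √(1 − ρ²). Power at 25 per arm:

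| ρ | effective d | power |
|---|---|---|
| 0.3 | 0.45 | 35% |
| 0.5 | 0.50 | 41% |
| 0.7 | 0.60 | 55% |
| 0.9 | 0.99 | 93% |

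Power of 90% needs ρ of nearly 0.9.

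**5. The planned repeated measures ANOVA.** For the group-by-time test with three visits, the noncentrality is (N/4) Σ(δⱼ − δ̄)² / (1 − ρ), where δⱼ is the group difference at visit j, 0 at baseline and 0.43 SD at 6 weeks. Over several patterns at 1 week and ρ from 0.3 to 0.7, power is about 19% to 50% at 25 per arm and 26% to 67% at 36.

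**6. Other readings of the inputs.**

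- One-sided 5% with 90% power needs 93 per arm; two-sided with 80% power needs 85 by the normal formula (86 by t).
- 0.43 as Cohen's f in a two-group comparison means d = 0.86: 29 to 30 per arm for 90%, and 85% power at 25.
- 0.43 as Cohen's f for the between-group factor over three visits gives 91.5% to 98.3% at 25 per arm for ρ of 0.7 down to 0.3. This assumes a difference of 0.86 SD at every visit, including baseline, where randomisation makes the expected difference zero.
- Entering f = 0.215 (half of 0.43) directly into the group-by-time formula gives 79.8% to 99.2%. Its noncentrality is 3 × 0.215² × N / (1 − ρ) = 0.139 N / (1 − ρ). A 0.43 SD difference at 6 weeks only gives 0.25 × 0.1233 × N / (1 − ρ) = 0.031 N / (1 − ρ). The ratio of 4.5 corresponds to a 6-week difference of 0.43 × √4.5 = 0.91 SD.

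The last two readings reach 90% only by making 0.43 stand for a difference about twice as large.

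**The case against.** The strongest reply is that no power equation was solved. The sentence presents 25 as a recommended pilot size, looked up by power, alpha and class of effect, so the 90% may be the power of the trial that the pilot is meant to inform. That is quite possible, and it cannot be settled without the cited source. It would explain the 25, but the sentence would then attach the 90% to the wrong trial.

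A second reply is that 32% belongs to a plain t test, not to the planned analysis, and depends on reading 0.43 as d. This stands as a limit on the single number, which should be printed only with its assumptions. It does not rescue the 90%, as steps 4 to 6 show.

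A third reply is that the Abstract, the Introduction and the Discussion all call the evidence preliminary, and that a mean difference with 95% CI is already promised. This stands too, and it weakens the consequence: a null result could be misread, not that it will be. The caveat nevertheless leaves the 90% uncorrected.

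A reader might infer three stronger things that the article does not support:

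- **That no two-arm comparison of means could give 90% at 25 per arm.** A baseline-adjusted analysis could, with a correlation near 0.9.
- **That the authors miscalculated.** The only visible arithmetic, 25 to 36, is right.
- **That the trial should have enrolled 115 per arm.** That would be the size for 90% power. It is not a requirement on a pilot.

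**Conclusion.** The point holds. As written, the Sample Size section gives this pilot a power that it does not have: about 32% at the 25 evaluable per arm that the plan expects, or 44% if all 36 per arm are analysed, against a stated 90%. These figures rest on 0.43 being a standardised mean difference and on an unadjusted two-sample comparison at two-sided 5%. With baseline adjustment at correlations of 0.3 to 0.7, the figure at 25 per arm is about 35% to 55%. Whether the fault is misattribution to the pilot or something else is open; the sentence needs correcting in either case. The harm is a possible misreading of the EPDS result, partly guarded against by the Discussion. The conduct of the trial is not affected.

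**What to change.** In Sample Size:

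- Remove 90% power as a property of this pilot, or say explicitly that it is the power of the future definitive trial to which the pilot recommendation refers.
- State the scale of 0.43.
- Give the pilot's approximate power with its assumptions: with 25 evaluable per arm, d = 0.43 and two-sided 5%, about 32% unadjusted and about 35% to 55% with baseline adjustment at correlations of 0.3 to 0.7.
- Give the expected 95% CI half-width, about 0.57 SD unadjusted.

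In Statistical Analysis, state that the EPDS difference will be interpreted from its estimate and 95% CI as input to the next trial, and that P>.05 will not be read as absence of effect.

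The change is to wording only. Recruitment is complete at 72, and enrolment does not change. The one cost is a less favourable stated power.

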### Statistical Analysis

Data will be analyzed using SPSS version 26, and significance is set at *P*<.05. Intention-to-treat analysis will be used. Categorical variables will be presented as the frequency and percent values, while continuous data will be presented as mean (SD). Baseline between-group comparisons will be conducted using Pearson chi square and Fisher exact tests for categorical data. Meanwhile, independent *t* tests will be used for continuous data. Repeated measures ANOVA will be used for within-group (time effect) and between-group (treatment effect) comparisons at 6 weeks. The mean difference and its corresponding 95% CI will be reported, with the significant level set at *P*<.05.

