#### Automatic Thought Questionnaire (ATQ)

The Automatic Thought Questionnaire (ATQ), which is available in the Malay language [56], assesses the frequency of negative automatic thoughts linked to depression and anxiety. This 17-item scale asks respondents to rate the occurrence of specific negative thoughts over the past week on a scale from 1 to 5. Higher total scores indicate more frequent negative thinking. The scale’s internal consistency ranges from 0.83 to 0.93 [56]. The total score ranges from 17 to 85, with a higher score reflecting a higher frequency of negative thinking.

Data are conducted at baseline, 1 week postpartum, and 6 weeks postpartum using the Google form, which is delivered via either the mobile app or a Whatsapp number. The self-reported survey takes approximately 15 minutes to 20 minutes to complete. All answers are automatically storied in the Google drive, and only the research team has access to the data. The schedule of enrollment, interventions, and assessments is summarized in Multimedia Appendix 4 and Multimedia Appendix 5.

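### The plan promises intention-to-treat, but its only outcome analysis, repeated measures ANOVA, would in standard form analyse only complete cases: about 50 of 72 mothers at the planned 30% nonresponse

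*Protocol article*

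**What the plan says.** Four statements in the protocol article bear on the point.

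- **Population** (Statistical Analysis): "Intention-to-treat analysis will be used".
- **Method** (same section): "Repeated measures ANOVA will be used for within-group (time effect) and between-group (treatment effect) comparisons at 6 weeks". The section names SPSS version 26 and gives no other analysis of the outcomes.
- **Waves** (end of the Automatic Thought Questionnaire section): "Data are conducted at baseline, 1 week postpartum, and 6 weeks postpartum using the Google form". The form reaches mothers through the app or through WhatsApp.
- **Expected loss** (Sample Size): "the suggested sample size per treatment arm based on previous literature with a medium effect size (0.43) [58] is 25", and then "a total of 72 participants (36 participants per arm) was required after taking into consideration a 30% nonresponse rate".

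The Results section reports that 36 mothers were enrolled in each arm.

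**The concern.** Standard repeated measures ANOVA works on one complete row per participant. In SPSS the usual procedure removes, listwise, anyone with a missing value at a time point in the model. The plan therefore fixes a method that leaves out randomised mothers as soon as forms go unreturned, and it expects a substantial share to go unreturned.

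Two things are at stake:

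- **The label.** Most readers take intention-to-treat to mean that all randomised mothers are included, not only that the arms are kept as allocated. An analysis of completers under that label would be read as stronger evidence than it is.
- **The information.** A mother who returns week 1 but not week 6 has an observed EPDS score that says something about her course, and the ANOVA discards it. Baseline EPDS is a poor substitute: eligibility restricts it to 9 to 11, so it barely separates one mother from another. Week 1 is the main observed outcome information on who was worsening before being lost.

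**Working it through.** **Inputs.** From Sample Size: 25 per arm before inflation, 30% nonresponse, 36 per arm and 72 in total after inflation. From Results: 36 + 36 enrolled. From the measurement text: three waves. The Abstract's Methods paragraph gives 64 mothers; I use 72, on which Sample Size and Results agree.

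**1. Reproduce the plan's figure.** Inflated n = n / (1 − loss) = 25 / (1 − 0.30) = 35.7, rounded up to 36 per arm, 72 in total. This matches. Because 36 per arm is also the number enrolled and allocated, the 30% is an allowance for loss among randomised mothers, not for refusals before entry.

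**2. Mothers left in a complete-case analysis at that loss.**

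- Per arm: 36 × 0.70 = 25.2, about 25.
- Total: 72 × 0.70 = 50.4, about 50.
- Left out: 72 − 50.4 = 21.6, about 22 randomised mothers.

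**3. Which mothers go, under two readings of the model.** The phrase about comparisons at 6 weeks does not settle which waves enter the ANOVA.

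| Mother's data | All three waves in the model | Baseline and week 6 only |
|---|---|---|
| Week 1 present, week 6 missing | dropped; week-1 score lost | dropped; week-1 score unused |
| Week 1 missing, week 6 present | dropped; week-6 score lost | kept |
| Both follow-ups missing | dropped | dropped |

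On either reading the mother lost by week 6 is removed and her week-1 EPDS plays no part. Only on the three-wave reading is a valid week-6 score also discarded.

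**4. Can the bias be sized?** Not from the article. As an illustration only, assume no true effect, an EPDS SD of 4, a correlation of 0.5 between week 1 and week 6, 30% loss at week 6, and log-odds of loss rising by 1 per SD of week-1 score where loss is score-related. The complete-case difference at week 6 (app minus control; negative favours the app) is then:

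- score-related loss in the app arm only: about −0.5 points;
- the same score-related loss in both arms: 0;
- score-related loss in the control arm only: about +0.5 points.

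The sign follows entirely from which arm is assumed to lose its worse-scoring mothers. None of these inputs is in the article.

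**The case against.** The strongest reply is that nothing here is contradictory. If intention-to-treat means only that mothers are analysed in the arm to which they were randomised, repeated measures ANOVA respects it. If missing values are imputed first, the ANOVA keeps all 72. The article does not name the SPSS procedure or mention listwise deletion, and missing-data rules are often left to an analysis plan that is not shown here. The study is also a pilot whose discussion already calls its findings preliminary.

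Much of this stands. A reader might infer that the two stated rules cannot both be followed; the documents do not support that, because either of those routes reconciles them. Silence on imputation is not in itself a fault in a condensed article. What remains is that the article does fix the method, and the method it fixes handles poorly the loss that the article itself expects.

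Three other inferences also go too far:

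- **Loss of 30% at each follow-up separately.** Sample Size uses the figure once, to go from 25 to 36 per arm. It reads as an overall allowance, and nothing supports compounding it.
- **Low power as a consequence of the deletion.** Whether 25 or 36 per arm is enough for an effect of 0.43 is a separate sample-size question, and it would remain with no missing data.
- **A spurious benefit for the app.** The response channel differs by arm, so differential loss is plausible. The article gives no ground for saying which arm would lose its worse-scoring mothers, and the illustration shows that the direction can reverse or vanish.

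**Conclusion.** The point holds as a mismatch between the promised population and the named method. It is not a logical contradiction. Run in standard form and without prior imputation, the ANOVA would use about 50 of 72 randomised mothers (about 25 per arm) and omit about 22, while being reported as intention-to-treat.

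The figure assumes that the planned 30% is realised, that it counts mothers missing at least one wave in the model, and that it is similar in the two arms. The exclusion itself needs only the standard behaviour of the procedure. Bias is possible if loss differs by arm, but its size and direction are unknown.

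For a pilot this is a should-fix. It still matters, because the plan tests at P<.05 and reports a mean difference with a 95% CI, which are likely to inform a later trial.

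**What to change.** 1. Replace repeated measures ANOVA with a likelihood-based linear mixed model, which SPSS offers as MIXED. Include arm, time and arm-by-time. Use every available baseline, week-1 and week-6 score from all 72 mothers in their allocated arm, and report the week-6 between-arm contrast with its 95% CI. Use the same model for the PoDLiS and ATQ scores. Multiple imputation by arm before the ANOVA is an acceptable alternative.
2. State the assumption plainly: the mixed model is valid if missingness depends only on observed data. A mother with a baseline score alone stays in the model but adds little about week 6.
3. Add one sensitivity analysis that shifts the missing week-6 EPDS values, for example by 1, 2 and 3 points in the app arm, and report where the conclusion changes.
4. If the ANOVA is kept without imputation, call it complete-case, say which waves it uses, and give the number analysed and the number excluded in each arm.

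The cost is a few sentences of analysis wording and a few hours of programming. No new data are needed. Since recruitment is complete, the change should be dated and recorded before outcomes are compared by arm.

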**Methods:**

This single-blinded, pilot randomized controlled trial includes 64 mothers recruited from the postnatal ward and randomized using a 1:1 ratio to receive either postpartum care (treatment as usual) or postpartum care (treatment as usual) plus the self-guided LoVE4MUM mobile app. The primary outcome is the effectiveness of the mobile app at improving postpartum depression. Secondary outcomes are changes in the mental health literacy score and negative automatic thoughts, which are collected using a self-reported questionnaire.

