### Recruitment

Mothers were recruited from the obstetric wards by the investigators. Mothers received comprehensive information about the study, including its aims, procedures, risks, and benefits. Sufficient time was given to ensure informed consent was obtained in the ward. Those agreeing to participate were enrolled in the pilot randomized controlled trial, and reasons for refusal were documented.

Patients were screened for eligibility based on the study criteria. Mothers (1) scoring between 9 and 11 on the EPDS, (2) who had access to a smartphone, (3) who possessed home wireless internet or could access internet connectivity, (4) who planned to continue routine postpartum care in the government primary health facility, and (5) who were literate in both English and Malay were included in the study. Mothers (1) with a history of drug abuse; (2) who had been diagnosed with depressive illness in the current pregnancy; (3) who were undergoing treatment for depression, bipolar disorder, or any other psychiatric disease at the time of participation; and (5) whose infant experienced intrauterine death or death immediately after birth were excluded from the study.

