## Results

Participant recruitment began on September 1, 2024. As of January 1, 2025, recruitment was complete, resulting in a total of 72 participants enrolled: 36 in the intervention group and 36 in the control group. Data analysis and results are anticipated to be available by March 2025. The trial results are expected to be published by the end of 2025.

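### The only named outcome model uses no baseline covariate, so the 6-week ATQ and PoDLiS estimates are probably less precise than the collected data allow

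*Protocol article*

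**What the plan says.** The protocol article (Methods, Statistical Analysis) gives a single outcome model: "Repeated measures ANOVA will be used for within-group (time effect) and between-group (treatment effect) comparisons at 6 weeks". It promises a mean difference with a 95% CI. It also tests the arms against each other at baseline but does not adjust for baseline.

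The end of the ATQ section sets the measurement times: "Data are conducted at baseline, 1 week postpartum, and 6 weeks postpartum using the Google form". Baseline ATQ and PoDLiS scores should therefore exist. The Abstract words the secondary endpoints as changes: "Secondary outcomes are changes in the mental health literacy score and negative automatic thoughts".

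Recruitment restricts entry to mothers "scoring between 9 and 11 on the EPDS". No such limit applies to ATQ or PoDLiS.

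The Sample Size section takes 25 per arm "based on previous literature with a medium effect size (0.43) [58] is 25" and concludes that "a total of 72 participants (36 participants per arm) was required after taking into consideration a 30% nonresponse rate". Results reports 36 enrolled in each arm.

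**The concern.** A baseline score can enter the analysis as one more level of the response or as a covariate. In a repeated measures ANOVA with time and group, it is a response level. The relevant treatment contrast for week 6 is then the group difference in change from baseline, which subtracts the whole baseline score whatever its correlation with follow-up. Covariate adjustment subtracts only the part of the baseline score that predicts follow-up, so its residual variance is never larger.

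The Introduction lists mental health literacy and negative thoughts among the targets for preliminary effectiveness. In a small pilot, the interval around each 6-week difference is the main product, so it matters if the named model makes that interval wider than the data require.

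**Working it through.** **Inputs**
- From Sample Size: effect size d = 0.43, two-sided alpha 0.05, 25 evaluable per arm, 30% nonresponse. The article does not tie the 0.43 to ATQ or PoDLiS; applying it to them as a standardised mean difference is an assumption.
- From Results: 36 per arm enrolled.
- Assumed: baseline-to-week-6 correlation rho from 0.3 to 0.7 (the article gives none), and equal SDs at the two times.

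**The plan's own figure.** 25 / (1 − 0.30) = 35.7, rounded up to 36 per arm and 72 in total. This reproduces.

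**Variance, in units of the week-6 variance**
- Change from baseline: 2(1 − rho).
- Baseline-adjusted: 1 − rho².
- Ratio, adjusted to change: (1 − rho²) / [2(1 − rho)] = (1 + rho)/2.

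The relative interval width is the square root of the ratio:

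| rho | Change | Adjusted | Ratio | Interval narrower by |
|---|---|---|---|---|
| 0.3 | 1.40 | 0.91 | 0.65 | 1 − √0.65 = 19% |
| 0.5 | 1.00 | 0.75 | 0.75 | 1 − √0.75 = 13% |
| 0.7 | 0.60 | 0.51 | 0.85 | 1 − √0.85 = 8% |

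This step does not use the effect size.

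**Power.** Noncentral t with noncentrality (d/√variance) × √(n/2). Degrees of freedom are 2n − 2 for the change contrast and 2n − 3 for ANCOVA. With d = 0.43:

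| n per arm | rho | Change | ANCOVA | Gain (points) |
|---|---|---|---|---|
| 25 | 0.3 | 24.2% | 34.5% | 10.3 |
| 25 | 0.5 | 31.9% | 40.5% | 8.6 |
| 25 | 0.7 | 48.5% | 55.0% | 6.4 |
| 36 | 0.3 | 33.0% | 47.0% | 14.0 |
| 36 | 0.5 | 43.6% | 54.7% | 11.0 |
| 36 | 0.7 | 64.2% | 71.2% | 7.0 |

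Gains come from unrounded powers. The ANCOVA column leaves out the small extra variance from estimating the slope. Multiplying its variance by 1 + 1/(2n − 4) lowers each gain in the table by less than 1 point.

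**Sensitivity**
- Other effect sizes, 36 per arm, rho 0.3 to 0.7: the gain is 7.5 down to 5.3 points at d = 0.3, and 13.2 down to 0.6 at d = 0.8.
- If the treatment test is an unadjusted week-6 contrast instead, the adjusted-to-unadjusted variance ratio is 1 − rho² = 0.91 to 0.51. The gain at d = 0.43 is then 2.6 to 23.0 points (25 per arm) or 3.4 to 27.6 (36 per arm).
- The omnibus group-by-time test and the group main effect averaged over all three times were also tried. ANCOVA had more power in every scenario computed.

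**EPDS.** Entry allows only the values 9, 10 and 11. If these are equally frequent, the baseline SD is √(2/3) = 0.8. With an assumed unrestricted SD of 4 to 5 and correlation of 0.5, simulation puts the correlation within this range at about 0.09 to 0.12. Power at 25 per arm then moves only from about 32.0% to 32.3%.

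**The case against.** **The premise is partly inferred.** The article does not list which times enter the ANOVA or which term is the treatment test, and a fuller protocol or SAP could add covariates. This stands as a limit on certainty. It does not remove the point, because the article does commit to a model for the 6-week treatment effect. The three waves, the time effect and the endpoints worded as changes all make baseline as a repeated level the natural reading.

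**The power figures are conditional.** This stands in full. The correlation is assumed and the 0.43 is borrowed. The upper range also needs all 36 per arm analysed, although the plan allows for 30% nonresponse.

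**The change analysis is valid and matches the endpoint wording.** This also stands. A reader might infer that chance baseline imbalance biases the result, or is a second defect. It is neither. Under randomisation the change contrast is unbiased, and the effect of chance imbalance is already counted in its variance.

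**The stakes are modest.** A reader might infer that the primary outcome suffers too. It does not, because the EPDS entry restriction leaves almost nothing to gain. What remains is precision on two secondary outcomes in a pilot that the Discussion itself calls preliminary, with power well short of 90% under either method at d = 0.43.

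**The fix may not be available as it stands.** The ATQ section delivers the form through the app or WhatsApp, and Randomization and Blinding says the allocation envelope's QR code opens those same channels. Baseline ATQ and PoDLiS might therefore have been completed after allocation. The article does not settle this, so it has to be checked.

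**Conclusion.** The point holds as a matter of efficiency for ATQ and PoDLiS. The named model has no baseline covariate, and adjusting for a baseline score taken before allocation would give confidence intervals about 8 to 19% narrower than a change-from-baseline contrast. That figure assumes equal SDs, rho between 0.3 and 0.7, and the change-contrast reading of the analysis sentence.

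The power gain is about 6 to 10 points at the planned 25 evaluable per arm and 7 to 14 points if all 36 are analysed. It further assumes that 0.43 applies to these outcomes, and it differs at other effect sizes. It should not be quoted as a fixed property of the plan.

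The documents do not support a claim of systematic bias or of a loss on the EPDS. The change is worth making because it is cheap and gives a better estimate from data already scheduled for collection.

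**What to change.** 1. Before arms are compared, confirm from the form time stamps or study procedures that the baseline ATQ and PoDLiS were completed before the envelope was opened. A score taken after allocation should not be used as the covariate.
2. If confirmed, amend Statistical Analysis so that the 6-week treatment effect on ATQ and PoDLiS is estimated by ANCOVA with the mother's own baseline score as covariate. A mixed model over weeks 1 and 6 with a week-6 contrast would serve equally well. Report the adjusted mean difference with its 95% CI.
3. Use the same form for the EPDS, with the screening score as covariate. This is for consistency only; no material gain is expected.

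The cost is the check in step 1, about one sentence of analysis text, and one degree of freedom per model. It needs no further mothers or visits, and the models are available in SPSS 26.
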